## INTRODUCTION

Chronic insomnia is a kind of sleep continuity disorder, accompanied by a series of daytime complaints such as sleepiness, fatigue, mood disorders or cognitive disorders, and sleep concerns and dissatisfaction with sleep, which affects up to a third of the adult population worldwide. Insomnia is the cause of many mental illnesses, and studies have shown that insomnia can increase the body's anxiety levels by 30% in the next day. Adequate, quality sleep can help people stay calm and reduce stress levels. At present, the main treatment methods of insomnia are pharmacological therapy, cognitive behavioral therapy and physical therapy, etc. Although pharmacotherapy and cognitive behavioral therapy for insomnia (CBT-I) therapy have made some advances, not all patients with insomnia respond to the recommended therapeutic options of CBT-I and pharmacological treatments. Therefore, it is necessary to develop new alternative therapies.

As a non-pharmacological therapy, transcutaneous auricular vagus nerve stimulation (taVNS) has been applied in the treatment of depression, epilepsy, migraine and other diseases. It can not only improve the insomnia symptoms of patients with depression, but also play a great role in the treatment of insomnia. A number of previous studies have shown that taVNS can not only effectively improve the sleep quality of insomnia patients, but also relieve their accompanying anxiety, depression, daytime sleepiness and fatigue symptoms. Therefore, taVNS may offer a novel potential treatment modality for insomnia.

Stimulation parameters, such as frequency, intensity and treatment course, are the key factors affecting the clinical efficacy of taVNS. Previous studies have verified that different frequencies of taVNS can produce different physiological responses, clinical efficacy and brain effect mechanisms. Different current intensities of taVNS also produce different physiological and clinical effects. Although the initial clinical results of taVNS in the treatment of insomnia are encouraging, the stimulation parameters of the existing studies are relatively uniform, all of which are disperse-dense wave, 4/20Hz, and the stimulation intensity is mainly tolerated by patients without pain. The treatment course is 4 weeks, and the follow-up is 2 weeks to 6 weeks. Therefore, the factors influencing the clinical efficacy of taVNS for insomnia remain unclear.

A number of previous studies have found an inverted-U response relationship between the efficacy of VNS and increased stimulus intensity. However, there are relatively few studies on the effect of taVNS stimulus intensity on clinical efficacy, and the results of these studies are inconsistent. Therefore, on the basis of verifying the efficacy and safety of taVNS in the treatment of insomnia, this study further investigated whether the stimulus intensity of taVNS affected the efficacy of ID, and whether there is a difference in efficacy between high and low intensity stimulation.

## HYPOTHESIS AND AIMS

The working hypothesis of the proposed study is that taVNS treatment for 8 weeks can significantly improve clinical outcomes in patients with insomnia, and the efficacy can be maintained for 3 months. To test this hypothesis, a 8-week, randomized controlled trial will be conducted in patients with insomnia to evaluate the efficacy of transcutaneous auricular vagus nerve stimulation (taVNS) on the clinical efficacy of insomnia patients, and to observe the 3-month efficacy of taVNS in the treatment of insomnia.

## PLAN OF INVESTIGATION

**Outline:** A randomized controlled trial is designed to test the clinical efficacy of taVNS in the treatment of insomnia for 8 weeks and whether the efficacy can last for 3 months. To achieve this objective, 72 patients with insomnia will be recruited and randomly assigned to receive taVNS treatment (n =36) or sham taVNS treatment (n = 36) for 8 weeks and 12-weeks followed up. The primary outcome is Pittsburgh Sleep Quality Index (PSQI) score. Secondary and exploratory outcomes include PSQI components, response rate, Insomnia Severity Index (ISI), 17-item Hamilton Depression Scale (HAMD-17), 14-item Hamilton Anxiety Scale (HAMA-14), Epworth Sleepiness Scale (ESS), Flinders Fatigue Scale (FFS) and adverse events. The trial will be conducted in compliance with the protocol, Good Clinical Practice (GCP) and the applicable regulatory requirement(s).

### Subjects

Diagnostic criteria: It meets the diagnostic criteria for insomnia disorder in the fifth edition of the Diagnostic and Statistical Manual of Mental Disorders (DSM-5).

1) Significant dissatisfaction with the quality or quantity of sleep, accompanied by at least one of the following symptoms:

- ①difficulty falling asleep;
  - ②difficulty in sleep maintenance, characterized by frequent awakening or difficulty falling asleep after awakening;
  - ③ Can't fall asleep again after waking up early.
- 2) Disturbed sleep (or associated daytime tiredness) causes significant distress or impairment in social, work, educational, academic, behavioral, or other important functions.
- 3) Sleeping difficulties occur at least 3 times a week.
- 4) Difficulty sleeping even when you get enough sleep opportunity.
- 5) Insomnia is not better explained by other sleep-wake disorders, nor does it occur during the course of other sleep-wake disorders (e.g., narcolepsy episodes, respiration-related sleep disorders, sleep-wake rhythm disorders, and parasomnia).
- 6) Insomnia is not caused by physical effects of substances (such as drug abuse).
- 7) Co-existing psychiatric and medical conditions are not sufficient to explain significant complaints of insomnia.

**Inclusion criteria:**

- 1) Meets the diagnostic criteria of DSM-5 insomnia disorder;
- 2) Insomnia symptoms lasting more than 3 months;
- 3) Chinese males and females aged 18 to 70 years;
- 4) Pittsburgh Sleep Quality Index (PSQI) score  $\geq 8$ ;  $7 \leq$  HAMA score  $\leq 14$ ,  $7 \leq$  HAMD score  $\leq 17$ ;
- 5) Didn't take any drugs or substances that act on the nervous system in the past month, and did not receive acupuncture treatment;
- 6) Can receive the treatment of auricular electrical stimulation;
- 7) Sign the informed consent.

- Exclusion criteria:**
- 1) Patients with severe physical diseases, such as coronary heart disease, malignant tumor, renal failure, etc.;
  - 2) Patients with organic brain diseases;
  - 3) with any other mental disorder, personality disorder or psychoactive substance abuse or dependence;
  - 4) Patients who cannot be eluted by drugs or acupuncture;
  - 5) Pregnant and lactating women;
  - 6) Ear skin damage;
  - 7) Unwilling to sign the informed consent form.

**Estimation of sample size**

This study was a prospective exploratory study. Using PSQI as the primary outcome and intervention and control group allocated as 1:1). Estimation of sample size is based on the results of the preliminary study, the mean PSQI score of patients with chronic insomnia is 14.9 (SD, 4.3), and the PSQI score is expected to be reduced to 11.1 after 8-weeks of taVNS treatment. Considering the dropout and loss to follow-up rate of approximately 25%, and with 0.05  $\alpha$ -level and 90% power, the total sample size required for the trial is 72 patients.

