## **Data analyses**

The analysis will be performed on the intention-to-treat (ITT) population that participants had been randomized. All efficacy analyses will be performed using the ITT analysis set and PP analysis set, defined as all randomized participants who received at least 6-week intervention. A mixed model for repeated measures (MMRM) with likelihood-based modeling to handle missing data will be applied to compare the primary outcome and secondary outcomes: change in the PSQI, ISI, HAMD, HAMA, ESS, FFS scores from baseline to week 4, 8, and 20. The model includes terms for treatment (taVNS or sham taVNS), visit (weeks 4, 8, 20), treatment by visit interaction, and baseline scores. Least squares mean change from baseline and least square mean difference between the groups at week 8 along with 95% confidence interval and a 2-sided p value will be estimated for the primary end point. Cohen d effect size will be calculated using the absolute value of the least square mean difference between groups in score from baseline at week 8 divided by the pooled SD estimated from the mixed model for repeated measures. For the PSQI responder analysis, the responder is defined as a 50% decrease at the end of treatment compared with baseline, which is prespecified in the statistical analysis plan. The percentage of PSQI responder at week 4, 8 and 20 will be calculated and summarized by treatment group. The percentage of PSQI responders at week 8 and 20 will be compared between groups using the Chi-square test. SAS, version 9.4 (SAS Institute Inc) is used for all analyses, with significance set at  $P < 0.05$ .

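### The sample size is built on the taVNS arm's own expected fall of 3.8 PSQI points, with no sham change stated, while the primary test is the difference between arms at week 8

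*Protocol*

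**What the plan says.** The section Estimation of sample size takes its figures from earlier work: "Estimation of sample size is based on the results of the preliminary study". It gives one mean, "the mean PSQI score of patients with chronic insomnia is 14.9 (SD, 4.3", and one expected value under treatment: "the PSQI score is expected to be reduced to 11.1 after 8-weeks of taVNS treatment". It then allows for a "dropout and loss to follow-up rate of approximately 25%, and with 0.05" alpha, and concludes with "90% power, the total sample size required for the trial is 72 patients". Allocation is 1:1. The section gives no expected week-8 score or change for the sham arm, and no between-group difference.

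The section Data analyses sets a different contrast for the primary endpoint. A mixed model for repeated measures, with baseline score as a term, estimates the "least square mean difference between the groups at week 8" with a 95% confidence interval and a two-sided p value.

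Under Treatment procedure, sham patients receive stimulation at the same ear sites and on the same schedule, at 0.1 mA. The Introduction describes the question as "whether there is a difference in efficacy between high and low intensity stimulation".

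**The concern.** A power statement belongs to the contrast it was computed for. Here the only effect quoted is a change within one arm, while the trial will be judged on the difference between two arms. Any improvement under sham comes straight off the 3.8 points.

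The protocol's own design gives no reason to expect no change under sham. Participants are blinded and told that they have an equal chance of either treatment. They apply a device that delivers a low current at the same sites for eight weeks. The stated aim of comparing high with low intensity leaves open whether low intensity has some effect.

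At stake is how the result is read. If the between-group difference at week 8 is not significant, the protocol as written invites the reading that a trial with 90% power found nothing. The actual power for a plausible between-group difference may have been well below that.

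**Working it through.** **Inputs.** From Estimation of sample size: mean 14.9, SD 4.3, expected taVNS value 11.1, alpha 0.05, power 90%, loss 25%, allocation 1:1. From Data analyses: two-sided test, between-group contrast at week 8, baseline score in the model. Sham change and the correlation between baseline and week 8 are not given, so both are assumptions below.

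**Step 1: reproduce 72.** Within-arm fall: 14.9 − 11.1 = 3.8. Use this as the between-arm difference in the two-sample normal formula:

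n per arm = 2 × (1.960 + 1.282)² × 4.3² / 3.8² = 26.9, rounded up to 27.

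Allow for loss: 27 / (1 − 0.25) = 36 per arm, 72 in total. This is the stated figure exactly.

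Other conventions do not give 72:

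- one-sided: 22 per arm, about 60 in total
- two-sided t-test: 28 per arm, 75 to 76 in total
- multiplying by 1.25 in place of dividing by 0.75: 68 in total
- one-sample (paired) formula with 4.3 as the SD of change: 14 before loss

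So the contrast entered was 3.8 in full, with nothing subtracted for sham.

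**Step 2: power when sham improves.** Let s be the sham improvement, so the between-arm difference is 3.8 − s. Power is from the noncentral t distribution with 27 per arm (52 degrees of freedom) and noncentrality (3.8 − s)/SD × √(27/2). The adjusted column uses a residual SD of 4.3 × √(1 − 0.5²) = 3.72, at an assumed correlation of 0.5.

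| Assumed sham improvement | Between-arm difference | Power, SD 4.3 | Power, SD 3.72 |
|---|---|---|---|
| 0 | 3.8 | 89% | 96% |
| 0.5 | 3.3 | 79% | 89% |
| 1.0 | 2.8 | 65% | 77% |
| 1.5 | 2.3 | 49% | 61% |
| 2.0 | 1.8 | 33% | 41% |

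The first entry is 89% and not 90% because the t distribution is used; the normal formula gives 90.1%.

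**Step 3: difference that 27 per arm can detect.** Same method, solved for the difference:

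| Analysis | 90% power | 80% power |
|---|---|---|
| Unadjusted, SD 4.3 | 3.9 (3.87) | 3.3 (3.34) |
| Adjusted, SD 3.72 | 3.3 (3.35) | 2.9 (2.89) |

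On the unadjusted inputs there is no room for sham improvement. On the adjusted ones there is room for 3.8 − 3.35 = 0.45, about half a point.

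**The case against.** The strongest reply is that the unadjusted calculation is too harsh on the trial. The planned model includes baseline score, and the 25% loss may fall partly after week 8, since follow-up runs to week 20. Both points stand. With all 36 per arm retained and SD 4.3, power is about 90% at a sham improvement of 0.5 and 78% at 1.0. With 27 per arm and an assumed correlation of 0.7 (SD 3.07), it is about 91% at 1.0, 77% at 1.5 and 56% at 2.0. A reader might therefore infer from the reproduced total that 90% power requires no sham improvement whatever. That is true only on the unadjusted inputs with 27 evaluable per arm. These margins do not replace a stated sham assumption, and the sample-size section invokes neither of them.

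A second reply is that the sponsor may have deliberately assumed an unchanged control. The match at 72 cannot rule this out: it shows which contrast was entered, not why. The arithmetic itself is correct. What is at fault is an assumption that is neither stated nor defended.

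A third is that the study is labelled exploratory. The same section nevertheless claims 90% power and a required total, and the section Purpose and potential says that a positive result would give direct evidence for an effective therapy.

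Two arguments for a sizeable sham fall are weak and are not relied on. The entry threshold of PSQI 8 lies (14.9 − 8)/4.3 = 1.6 SD below the stated mean, so regression to the mean caused by that threshold should be small. Sleeping pills are allowed only temporarily and within limits, and participants are encouraged to avoid them.

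**Conclusion.** The point holds in this form: the claimed 90% power rests on an unstated assumption of zero sham improvement, because the taVNS arm's own fall stands in for the between-group difference that will be tested. Its size depends on the sham change, which the protocol does not give. At an assumed 1.0 point, power is 65% unadjusted and 77% with baseline adjustment at an assumed correlation of 0.5. At 2.0 points it is 33% and 41%. Both sets assume 27 evaluable per arm at week 8.

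A reader might go further and conclude that the trial's real power is no better than a coin toss. The document does not support that: it corresponds to one assumed case, a sham improvement of 1.5 points with no baseline adjustment. Nor does it follow that 72 patients are too few, since the protocol states no between-group difference against which to judge this. The planned week-8 estimate and its confidence interval remain valid in any case.

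**What to change.** Keep the total at 72 and rewrite the sample-size paragraph.

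- Remove the claim that 72 patients give 90% power on the basis of a fall to 11.1 under taVNS.
- State instead what 27 evaluable patients per arm can detect between groups at week 8: about 3.9 points with 90% power and 3.3 with 80%, at SD 4.3 without adjustment. If the planned baseline adjustment is to be credited, give about 3.3 and 2.9, and name the assumed correlation of 0.5.
- State the sham change assumed and the reason for it, drawing on the preliminary study if it had a suitable control arm.
- Add a short table of power against sham change, as in the working.

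The cost is one rewritten paragraph and a small table, with no extra patients and no change to endpoint or analysis. The downside is that the stated power becomes less favourable, and the sponsor will have to defend the between-group difference that it hopes to see.

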**Screening, randomization and blindness**

Eligible patients will be recruited from hospital outpatient clinics at Acupuncture and Moxibustion Hospital, China Academy of Chinese Medical Sciences (CACMS). If the recruitment could not reach the goal as the designed timetable frame at the end of the first year, additional study sites or other means of recruitment methods, such as advertisement, hospital WeChat official account and posters, will be considered to be included.

Screening will be conducted by the principal investigator following the inclusion and exclusion criteria. Randomization will be performed by an independent statistician in blocks with the use of SAS (version 9.4) software, with a block length of four. The randomized contents will be bound in closed envelopes,

and the order of each envelope is marked, which will be kept by a research assistant, but inaccessible to other study personnel. Remove envelopes according to the order in which the patients are enrolled.

After patient's eligibility is confirmed, patients will be randomly assigned to taVNS group or sham taVNS group in a ratio of 1:1 by informing as follows: "you will be randomly assigned to taVNS or sham taVNS treatment for your insomnia syndrome. You will have an equal chance to be assigned in either group, but either you or we will not know which group you will be assigned until investigational treatment completes." Clinical investigators, care providers, lab technicians, and data analysts will be blind to patients' treatment condition. The success of blinding will be tested by asking all participants the following question after the completion of the investigational treatment: "When you volunteered for the trial, you were informed that you had an equal chance of receiving taVNS or sham taVNS treatment. Which do you think you received?"

To assess the blinding maintenance of this study, the Bang's blinding index will be estimated. The primary purpose of BBI is to quantitatively evaluate the effectiveness of blinding. BBI assumes that in the absence of any unblinding, participants will guess their treatment group at random. For instance, in this two-arm trial (taVNS vs. sham taVNS), participants would have a 50% chance of guessing correctly purely by chance. The assumption also implies that each participant's guess is independent of others' guesses. This means that the blinding effectiveness is evaluated based on individual guesses without considering potential patterns or correlations between different participants' guesses. If the blinding is effective, the proportion of correct guesses should align closely with the expected proportion under random guessing. A higher than expected proportion of correct guesses suggests potential unblinding, meaning participants might have received cues or information that helped them correctly identify their treatment allocation. Conversely, a lower than expected proportion of correct guesses could indicate systematic bias or misinformation. As a statistical measure designed to assess the success of blinding in clinical trials, the estimation of BBI has been previously described in detail. In short, the BBI estimates the proportion of individuals who guess their treatment assignment correctly in the  $n$ th treatment arm. Each arm of a trial will therefore have its own BBI value, which is a continuous value and takes on a value between -1 and 1. If the BBI equals 1, it means that all responses are correct, and complete unblinding is inferred. If the BBI equals -1, then all responses are incorrect, and complete blinding is Inferred, although this may indicate unblinding in the opposite direction (e.g. opposite guessing). If the BBI equals 0, then half of the guesses are correct and half of the guesses are incorrect, inferring random guessing. In general, if the BBI takes on value from -0.2 to 0.2, blinding is considered to be successful. Unblinding (or opposite guessing) may be claimed if the relevant limit of the 95% confidence interval does not cover 0.

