#### **Treatment procedure**

The intervention protocol was based on a preliminary clinical trial, utilized an electroacupuncture instrument (Hwato, SDZ-II B, Suzhou, China) and special silica gel ear clips. Patients in both groups received electrical stimulation at the bilateral auricular cymba conchae(auricular point kidney, CO10) and cavum conchae(auricular point heart, CO15), where there is rich of vagus nerve distribution. Patients in taVNS group received stimulation parameters, including dilatational wave at 4/20Hz (4Hz for 5 seconds, 20Hz for 10 seconds, alternately), pulse width of 0.2ms±30%, and intensity adjusted to the patient's maximum tolerable level (0.8~1.5mA). The sham taVNS group received the same parameters with a current intensity of 0.1mA.

On the day of enrollment, each patient will be taught to use the instrument, informed of precautions, and ensure that each patient could treat himself at home. Patients in both groups start treatment on the day of randomization and bilateral auricles receive stimulation simultaneously for 30 min each time, twice a day, five consecutive days a week, for 8 weeks, followed by a 12-week observational period. Sleep treatment diary will be used to monitor the patient's treatment and sleep status.

Patients are encouraged to avoid using medications or other therapies for treatment of insomnia throughout the trial. In accordance with the Declaration of Helsinki, if patients have severe insomnia and affect their daily life, temporary use of sleeping pills is allowed (the frequency of continuous use of drugs is allowed to be less than 3 nights), and the name and dose of drugs are recorded in the sleep diary and informed to the responsible doctor. For those who were under anti-hyperlipidemic, antihypertensive and anti-diabetic treatment, they were allowed to continue their current medications throughout the study. Drug history of the participant will be systematically recorded in the case report form.

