## Clinical and biochemical assessment

Efficacy: The efficacy of the taVNS for chronic insomnia disorder will be associated with the primary outcome and secondary outcome.

The primary outcome is PSQI. The primary endpoint is the mean changes from baseline through week 8 in PSQI scores.

Secondary outcomes include the mean changes in PSQI scores at 4, 20 weeks, the response rate at 4, 8 and 20 weeks, as well as the changes in seven components of PSQI, Insomnia Severity Index (ISI), Hamilton Depression Scale (HAM-D-17), Hamilton Anxiety Scale (HAM-A-14), Epworth Sleepiness Scale (ESS), and Flinders Fatigue Scale (FFS) from baseline to 4, 8 and 20 weeks. Adherence is monitored through the sleep treatment diary. Additionally, adverse reactions are recorded. The response rate was defined as the percentage of patients with a reduction of  $\geq 50\%$  from baseline in the PSQI score after treatment.

Other clinical assessments will be conducted at baseline, 4 weeks, 8 weeks and 20 weeks. Blood pressure will be measured by clinical sphygmomanometer with the cuff placed around the upper arm. It will be measured in the morning at resting state after sitting quietly for at least 15 minutes. The measurement will be conducted in the same arm and no talking will be allowed during the measurement.

Safety: The safety of the taVNS will be associated with adverse events (AEs) reported by participants and recorded by physician. The incidence, intensity, subjective feeling of the relationship with the treatment, and management of the event will be recorded. Safety assessment will be conducted at 4 weeks, and 8 weeks. The reasons for withdrawal will be recorded when a subject withdraws before completing the study. Serious AEs are defined as any undesirable experience that is fatal, is life-threatening, requires initial or prolonged in-patient hospitalization, or causes persistent or significant disability or permanent damage.

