### 321 322 **Procedures for Discontinuation or Withdrawal of a Subject**

323 The investigator may terminate a subject's study participation at any time during the study when the  
324 subject meets the study termination criteria. In addition, a subject may discontinue his or her  
325 participation without giving a reason at any time during the study. Should a subject's participation be  
326 discontinued, the primary criterion for termination would be recorded. Subjects who discontinue the  
327 study during the double-blind treatment period will visit the site as soon as possible for clinical  
328 assessment if applicable. Discontinued or withdrawn subjects will not be replaced.

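### The patient script promises blinding only until treatment ends at week 8, and no other text clearly carries the blind to the week-20 assessment on which the durability hypothesis rests

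*Protocol*

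**What the plan says.** Under Screening, randomization and blindness, the protocol fixes the words used with each patient: "either you or we will not know which group you will be assigned until investigational treatment completes". The next sentence of that section says that clinical investigators, care providers, laboratory technicians and data analysts are blind, without saying for how long. Patients are asked to guess their arm after treatment completes, and no repeat of the question is scheduled.

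Treatment procedure sets stimulation "for 8 weeks, followed by a 12-week observational period".

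Unblinding Procedures forbids the investigator to break the blind unless the subject's medical treatment requires it. It gives no end date either.

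Hypothesis and Aims expects 8 weeks of taVNS to improve outcomes "and the efficacy can be maintained for 3 months". Clinical and biochemical assessment puts the primary endpoint at week 8. For later time points it states: "Secondary outcomes include the mean changes in PSQI scores at 4, 20 weeks, the response rate at 4, 8 and 20 weeks". The seven PSQI components, ISI, HAMD, HAMA, ESS and FFS follow, with changes "from baseline to 4, 8 and 20 weeks". Data analyses includes week 20 as a visit in the mixed model and compares week-20 responders by chi-square test.

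**The concern.** The only statement of how long a patient stays blind is the script, and it stops 12 weeks before the final assessment. Its wording covers the study team as well as the patient.

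Every efficacy outcome at week 20 is a questionnaire, a rating scale or derived from one. The section on assessments names no objective sleep measure to fall back on. A sham patient who learned the arm at week 8 might report worse sleep. The same patient might also turn to other treatment, since Treatment procedure only encourages patients to avoid it and permits temporary sleeping pills. A week-20 difference could then reflect expectation or changed behaviour instead of a lasting effect of stimulation. Once a patient has been told the arm, no analysis can restore the blind for that patient's week-20 data.

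**Working it through.** **Step 1: timeline.** Treatment runs from randomization to week 8 and observation adds 12 weeks: 8 + 12 = 20. Efficacy visits are at weeks 4, 8 and 20. One of the three follows the end of the promised blind, and it is the only one that bears on durability.

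**Step 2: the blinding statements side by side.**

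| Protocol section | Who is covered | Stated end |
|---|---|---|
| Screening, randomization and blindness, patient script | Patient and team | Completion of treatment (week 8) |
| Same section, following sentence | Investigators, care providers, lab technicians, data analysts; patients not named | None |
| Unblinding Procedures | Restrains the investigator; exception for medical need | None |

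If the two open-ended statements run to the end of the study, they conflict with the script. If they run only as long as the script, nothing protects week 20. Either way, the protocol does not say whether the blind still holds at week 20. For patients the only explicit statement is the script. For raters two open-ended statements stand against the words that include the team in the script, so the exposure of raters is the weaker half of the point.

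**Step 3: what depends on week 20.** Data analyses covers seven outcomes at that visit: PSQI change, PSQI response, ISI, HAMD, HAMA, ESS and FFS. The seven PSQI components are listed as week-20 outcomes but are not named in the analysis list.

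**Step 4: the plan's own sample size, reproduced.** Inputs from Estimation of sample size: PSQI 14.9 (SD 4.3), expected to fall to 11.1, alpha 0.05, power 90%, dropout 25%. The difference is 14.9 − 11.1 = 3.8, if sham stays at 14.9.
- n per arm = 2 × [(1.960 + 1.282) × 4.3 / 3.8]² = 26.9, rounded up to 27.
- With dropout: 27 / 0.75 = 36 per arm, 72 in total. This matches the protocol.

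**Step 5: illustration of the possible effect on a week-20 PSQI comparison.** Assume no true week-20 effect and a reporting shift b between arms caused by knowing the arm. The documents give no value for b. The standard error is 4.3 × √(2/n): 1.17 for n = 27 and 1.01 for n = 36. The rejection probability of a two-sided 5% t-test with noncentrality b/SE is:

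| Assumed shift b (PSQI points) | 27 per arm | 36 per arm |
|---|---|---|
| 0 | 5% | 5% |
| 0.5 | 7.0% | 7.8% |
| 1 | 13.4% | 16.4% |
| 2 | 38.9% | 49.5% |

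The SD of 4.3 is that of the raw score. The planned model uses baseline-adjusted change, whose SD is not given.

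**The case against.** The strongest reply is that the protocol never orders or schedules disclosure at week 8. No visit, person or procedure is named for telling patients their arm. The script promises ignorance up to a point and does not promise disclosure at that point. The rule in Unblinding Procedures has no exception for the end of treatment, and the staff-blinding sentence has no time limit. All of this stands. A reader might infer that patients and raters will be unblinded at week 8, but the text does not support that. It leaves the end of the blind open or in conflict.

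A reader might also infer that the primary result is compromised, because week-20 scores enter the same mixed model. The model has a treatment-by-visit interaction, so the week-8 contrast is driven mainly by week-8 data. Week-20 scores matter to it chiefly for patients who miss week 8 and return at week 20. That influence is indirect, and nothing in the document allows it to be sized.

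Nor does the label in "study during the double-blind treatment period will visit the site as soon as possible for clinical" settle when blinding ends. It names a study phase in a rule about early-discontinuation visits.

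Finally, the week-20 outcomes are secondary, the trial describes itself as exploratory, and the timing of final unblinding is often left to the statistical analysis plan. The first two considerations lower the severity. The third does not answer the point: what patients are told is protocol content, and an analysis plan cannot change it.

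**Conclusion.** The point holds as an unresolved end of blinding. The script sets it at week 8, the other statements set no end, and the protocol thereby permits the arm to become known before the week-20 assessment. It does not show that this will happen.

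What is exposed is the single post-treatment visit and, with it, the claim that "the efficacy can be maintained for 3 months". The week-8 primary endpoint is inside the promised blind, provided it is assessed before any disclosure. The exposure is clearer for patient-reported scales than for the rater-scored HAMD and HAMA.

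The severity is moderate. The false-positive rates of roughly 7% to 49% are illustrations for assumed shifts of 0.5 to 2 points and are not estimates of what this trial will show.

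**What to change.** In Screening, randomization and blindness, change both the script and the blinding text. They should say that patients, investigators, outcome raters and analysts remain blind until the last patient's week-20 assessment is complete and the database is locked. Give the rule in Unblinding Procedures the same end point. Leave the emergency unblinding route as it is.

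Leave the wording on early-discontinuation visits in Procedures for Discontinuation or Withdrawal of a Subject unchanged. Extending its phase label to follow-up would alter which subjects are called for that visit.

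The cost is a few sentences in the protocol and the matching patient information. Patients wait at least 12 weeks longer to learn their arm, and those enrolled early wait longer still, until the last patient has finished and the database is locked.
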